## Abstract

**Background:**

Based on high-quality evidence, guidelines recommend the long-term use of secondary prevention medications post-myocardial infarction (MI) to avoid recurrent cardiovascular events and death. Unfortunately, discontinuation of recommended medications post-MI is common. Observational evidence suggests that prescriptions covering a longer duration at discharge from hospital are associated with greater long-term medication adherence. The following is a proposal for the first interventional study to evaluate the impact of longer prescription duration at discharge post-MI on long-term medication adherence.

**Objective:**

The overarching goal of this study is to reduce morbidity and mortality among post-MI patients through improved long-term cardiac medication adherence. The specific objectives include the following. First, we will assess whether long-term cardiac medication adherence improves among elderly, post-MI patients following the implementation of (1) standardized discharge prescription forms with 90-day prescriptions and 3 repeats for recommended cardiac medication classes, in combination with education and (2) education alone compared to (3) usual care. Second, we will assess the cost implications of prolonged initial discharge prescriptions compared with usual care. Third, we will compare clinical outcomes between longer (>60 days) versus shorter prescription durations. Fourth, we will collect baseline information to inform a multicenter interventional study.

**Methods:**

We will conduct a quasiexperimental, interrupted time series design to evaluate the impact of a multifaceted intervention to implement longer duration prescriptions versus usual care on long-term cardiac medication adherence among post-MI patients. Intervention groups and their corresponding settings include: (1) intervention group 1: 1 cardiac center and 1 noncardiac hospital allocated to receive standardized discharge prescription forms supporting the dispensation of 90 days’ worth of cardiac medications with 3 repeats, coupled with education; (2) intervention group 2: 4 sites (including 1 cardiac center) allocated to receive education only; and (3) control group: all remaining hospitals within the province that did not receive an intervention (ie, usual care). Administrative databases will be used to measure all outcomes. Adherence to 4 classes of cardiac medications — statins, beta blockers, angiotensin system inhibitors, and secondary antiplatelets (ie, prasugrel, clopidogrel, or ticagrelor) — will be assessed.

**Results:**

Enrollment began in September 2017, and results are expected to be analyzed in late 2020.

**Conclusions:**

The results have the potential to redefine best practices regarding discharge prescribing policies for patients post-MI. A policy of standardized maximum-duration prescriptions at the time of discharge post-MI is a simple intervention that has the potential to significantly improve long-term medication adherence, thus decreasing cardiac morbidity and mortality. If effective, this low-cost intervention to implement longer duration prescriptions post-MI could be easily scaled.

**Trial Registration:**

ClinicalTrials.gov NCT03257579; https://clinicaltrials.gov/ct2/show/NCT03257579

**International Registered Report Identifier (IRRID):**

DERR1-10.2196/18981

## Introduction

### Background

International guidelines recommend the long-term use of secondary preventative cardiac medications following a myocardial infarction (MI) [1-3]. The medication classes used for secondary prevention post-MI include both a primary antiplatelet (aspirin) and secondary antiplatelet (eg, prasugrel, clopidogrel, or ticagrelor), statins, beta blockers, and angiotensin system inhibitors (ie, an angiotensin-converting enzyme inhibitor or angiotensin receptor blocker). These medications provide an expected 60% relative risk reduction of recurrent cardiovascular events [1,2]. However, studies have shown that postdischarge cardiac medication adherence tends to steadily decline over time (Figure 1) [4-12]. Multiple studies have shown an increased risk of morbidity and mortality associated with medication nonadherence in patients with coronary artery disease (CAD) [10-14].

**Figure 1 figure1:**
[figure not shown]
Persistence with secondary prevention medications after angiography. ACE: angiotensin-converting enzyme.

Although medication adherence is a complex phenomenon with multiple interacting factors, there is emerging evidence that a simple step taken by health care providers at the time of hospital discharge plays an important role in long-term adherence. In a population-based observational study of over 18,000 patients conducted by our research team, greater long-term adherence to cardiac medications was observed in Ontario patients receiving longer initial prescriptions (>60 days versus <31 days) at the time of discharge [4]. Specifically, a higher proportion of patients receiving longer duration prescriptions had greater than 80% proportion of days covered (PDC) in the 18 months following hospital discharge for angiotensin system inhibitors (adjusted odds ratio [OR] 4.1, 95% CI 3.6-4.7), beta blockers (adjusted OR 2.4, 95% CI 1.9-3.1), and statins (adjusted OR 3.0, 95% CI 2.6-3.4) [4]. Two earlier studies found similar results. Batal et al [15] analyzed a cohort of 3386 patients from a large US health care center and found higher adherence to statins in patients with mostly 60-day prescriptions as compared to those with mostly 30-day prescriptions (adjusted risk ratio 1.4, 95% CI 1.3-1.6). Steiner et al [16] examined maintenance of medication in 290 outpatients from Veteran Affairs Centers in the United States and found that those with longer prescriptions for digoxin (ie, at least a 90-day supply) were more likely to regularly acquire the medication over 9 to 14 months. While these 3 observational studies suggest an association between prescription duration and long-term medication adherence, evidence from a prospective study is required to support implementation of this policy as a best practice.

### Rationale and Study Objectives

Poor medication adherence was identified by the World Health Organization in 2003 as a worldwide challenge in the management of chronic diseases [17]. The consequences of suboptimal adherence include undesirable health outcomes as well as increased health care costs. Both provider-level and system-level factors play important roles in optimizing adherence. We have previously shown that inappropriate beliefs regarding risk perception and outcome expectancies, prescription refill burden, and unintentional forgetfulness due to lack of habituation all contribute to the observed general decline in medication adherence over time [18-20]. Providing longer prescriptions at the time of discharge can address all of these barriers. However, prescriptions covering ≥90 days are currently provided to only 21% of all cardiac patients and to no more than 54% of MI patients, suggesting an opportunity for this change to benefit many patients [4,21].

We know of no guidelines or practice standards for physicians that recommend the prescription of maximum duration (ie, ≥90 days) for cardiac medications at discharge. The use of standardized hospital-based medication discharge practices has been shown to minimize medication errors and to optimize guideline-recommended therapies [22]. However, no prospective study has evaluated the effects of implementing an institutional policy or standardized discharge cardiac medication prescriptions of maximum duration on long-term medication adherence. Therefore, it is hypothesized that longer prescription duration at discharge will promote better long-term cardiac medication adherence.

The specific objectives of this study include estimating and comparing the effects on long-term cardiac medication adherence of (1) a standardized discharge form featuring prescription duration of 90 days with 3 repeats in post-MI patients in combination with education, (2) education only, and (3) usual care (ie, no intervention regarding prescription duration) and assessing the economic implications of the prolonged initial discharge prescriptions as compared to usual care. To our knowledge, this project is the first interventional study to investigate how modifying prescription duration impacts medication adherence.

## Methods

### Trial Setting and Design

The Myocardial Infarction Prescription Adherence Duration (MIPAD) study will use a quasiexperimental, interrupted time series design to evaluate the impact of standardized prolonged discharge prescription forms and education versus usual care on long-term cardiac medication adherence among elderly, post-MI patients in Ontario who were discharged from hospital following a cardiac catheterization procedure between September 1, 2015 and August 31, 2018.

After the first 24 months within the study window (ie, the pre-intervention period: September 1, 2015 through August 31, 2017), a total of 6 sites (2 of which are cardiac centers, where advanced cardiac procedures are performed in Ontario) across 3 hospital corporations (Hamilton Health Sciences [HHS], St. Joseph’s Healthcare Hamilton, and Niagara Health System [NHS]) were nonrandomly allocated to receive at least one of the two planned intervention packages for the subsequent 12 months (ie, the post-intervention period: September 1, 2017 through August 31, 2018; Figure 2). These 6 intervention sites were chosen as a convenience sample based on the investigators’ affiliations. Irrespective of intervention package received (detailed fully in the following sections), all interventions were implemented starting September 1, 2017 at each of these sites. All 6 intervention sites are within the same health care region in southwest Ontario, Canada, which serves approximately 1.4 million people. All other Ontario hospitals will collectively act as a contemporaneous control group [23,24].

**Figure 2 figure2:**
[figure not shown]
Intervention and control groups in the Myocardial Infarction Prescription Adherence Duration (MIPAD) study.

### Intervention Packages

#### Groups

The MIPAD study team delivered a multifaceted intervention to reduce morbidity and mortality among post-MI patients through improving long-term adherence to secondary prevention medications. Intervention group 1, comprised of 1 cardiac center and 1 noncardiac hospital (both belonging to the same hospital corporation), received both revised standardized discharge prescription forms and education. Intervention group 2, comprised of the other 4 sites across 2 hospital corporations (including 1 cardiac center), received education alone. The remaining Ontario hospitals, comprising the parallel control group, did not receive any intervention (ie, usual care) [23,24]. The knowledge-to-action framework informed the hypothesis, intervention development, and evaluation of this study [25].

#### Standardized Discharge Prescription Forms

We implemented a revised standardized discharge prescription form available on all wards where MI patients are managed. The revised prescription form has a default of a 90-day supply with 3 repeats for recommended cardiac medications (ie, primary antiplatelet [aspirin], statin, beta blocker, angiotensin system inhibitor, and secondary antiplatelet). Current discharge prescription forms leave the dispensation amount and repeats to the discretion of the individual physician. To encourage community pharmacists to dispense 90 days’ worth of medications at discharge, in accordance with the revised discharge prescriptions, the Ontario Pharmacists Association recommended that the following statement be included on the discharge prescription: “Override trial dispensation as these medications were initiated in hospital, Use code NH.” This is a standard mechanism to ensure patients with drug coverage from a provincial payer (ie, the Ontario Drug Benefit [ODB] Plan) receive the correct amount of medications on their first fill post-discharge. See Figure 3 for a copy of the discharge prescription form and highlighted revisions. The intervention may be tailored by the physician to allow shorter discharge prescription durations for cost consideration in patients less than 65 years of age and without medication insurance. Monthly monitoring with intervention group 1 ward visits ensured standardized prescription forms were being implemented.

**Figure 3 figure3:**
[figure not shown]
Example discharge prescription from Hamilton Health Sciences with intervention revisions circled.

#### Education

The education-based intervention consists of both components detailed in the following sections.

For educational outreach to the hospital staff, educational rounds for all involved health care providers (eg, physicians, residents, nurses) at each of the 6 sites took place at the start of the intervention period to outline the evidence regarding longer prescriptions at discharge and encourage this change in discharge practices. In a preliminary survey of 82 health care providers in the study region, 95% said they would use standardized discharge prescriptions with 3 months of cardiac medication supplies and 3 repeats but less than 50% admitted that they currently provide medication supplies to cover a year ([name], unpublished data). Further education (eg, emails, mailouts, site visits) occurred every 3 months during the intervention period.

For educational support of community pharmacies, in addition to the statement “Override trial dispensation as these medications were initiated in hospital, Use code NH” added to the discharge prescriptions, outreach via personal emails and newsletters to community pharmacies in the study region was undertaken with help from the Ontario Pharmacists Association and Ontario Pharmacy Evidence Network. This outreach was intended to help ensure fidelity of the intervention when medications were dispensed at discharge.

### Data Sources

The following administrative databases held at ICES McMaster will be linked and analyzed for the MIPAD study: (1) CorHealth Cardiac Registry (CCN-CR), which is a clinical database containing information such as demographics, comorbidities (eg, diabetes, hypertension, prior heart disease), and procedure-specific details (eg, referral date, patient wait time, complications, results) for patients who undergo a cardiac procedure (eg, cardiac catheterization, percutaneous coronary intervention, or coronary artery bypass graft surgery) in Ontario [26]; (2) Canadian Institute for Health Information Discharge Abstract Database, which captures demographic, clinical, and administrative information on all hospital inpatient discharges (including deaths, sign-outs, and transfers) in all provinces and territories except Quebec; (3) National Ambulatory Care Reporting System, containing data for all ambulatory care provided in hospital (eg, day surgeries and emergency department visits) or in the community across Canada; (4) ODB database, which captures all prescription medication dispensations for Ontario residents covered under the ODB plan (including those aged 65 years and older); (5) Ontario Health Insurance Plan database, covering physician billings for procedures and consultations; and (6) Registered Persons Database, containing demographic information (including date of death) on all persons registered under the Ontario Health Insurance Plan, which is the majority of Ontario residents. The CCN-CR has been used for numerous quality assurance and research projects, including 1 observational and 1 randomized controlled trial (RCT) conducted by the principal investigators of the MIPAD study [4,27]. Several provinces and territories (including Ontario) also use the Canadian Institute for Health Information Discharge Abstract Database to capture day surgeries [28]. Of the 5 recommended cardiac medication classes post-MI, aspirin (primary antiplatelet) is poorly captured in the ODB, as most dispensations are private pay. Correspondingly, measurement of medication adherence in this study will only concern statins, beta blockers, angiotensin system inhibitors, and secondary antiplatelets.

### Recruitment

Our study population will consist of patients aged 65 years and older who were discharged home from an Ontario hospital between September 1, 2015 and August 31, 2018 following a cardiac catheterization post-MI with evidence of CAD [29]. First, we will identify any CCN-CR claims for a cardiac catheterization with the primary referral reason being a ST-elevation myocardial infarction (STEMI) or non-STEMI with evidence of CAD, defined as left main artery stenosis ≥50% or major epicardial coronary artery stenosis ≥70% (Multimedia Appendix 1) [29]. Patients will be excluded if they meet any of the following criteria: site of procedure missing on their index claim, invalid or missing health card number, non-Ontario resident, <65 years of age (ie, patients who are not automatically eligible for ODB due to age) or ≥105 years of age, or died prior to discharge. Lastly, we will restrict to patients who filled a prescription for at least one medication from one of the 4 recommended cardiac medication classes (ie, statin, beta blocker, angiotensin system inhibitor, or secondary antiplatelet) within 7 days of discharge. This 1-week window was specified based on pre-intervention data, which determined that 93.4% of patients meeting all other exclusion criteria filled at least one recommended cardiac medication within 7 days (with 87.2% having their first fill within 1 day of discharge). We will herein refer to this initial prescription fill as a patient’s index fill. If patients have multiple eligible index cardiac catherization claims within the accrual window — an uncommon occurrence based on pre-intervention data — we only include the patient’s first claim (ie, earliest by date). Figure 4 fully summarizes the application of eligibility criteria to accrue study participants within the pre-intervention period.

**Figure 4 figure4:**
[figure not shown]
Flow of participants into the study during the pre-intervention period (preliminary data used for power calculation). Notes: Patient age determined at procedure date – 120 days. CAD: coronary artery disease; CCN-CR: Cardiac Care Network – Cardiac Registry; CIHI-DAD: Canadian Institute for Health Information - discharge abstract database; MI: myocardial infarction; RPDB: registered persons database.

### Outcome Measures

#### Primary Outcome

The primary outcome will be long-term cardiac medication adherence assessed at 365 days from discharge. To calculate the primary outcome per patient, first we will identify the number of unique cardiac medication classes (out of 4) — statins, beta blockers, angiotensin system inhibitors, and secondary antiplatelets (ie, prasugrel, clopidogrel, or ticagrelor) — that were dispensed, as per ODB claims on the patient’s index fill date. The PDC will then be calculated per class [30,31], as it is generally a more conservative measure of adherence than the medication possession ratio [30,32]. If patients have 2 or more filled prescriptions for drugs in the same medication class with overlapping days supplied, we will assume the supply was used in sequence, as multiple doses of a drug in the same class would not typically be administered simultaneously [33]. The sum of class-specific PDC values across all classes will then be derived for each patient. Patients with an average PDC ≥80% among those medication classes dispensed at their index fill will be considered as adherent to their cardiac medication regimen [34]. For patients who die during their 1 year of follow-up, their PDC per class will be calculated over the time elapsed (in days) between their index fill and death date. It is not expected that this intervention will increase the number of cardiac medications prescribed to post-MI patients at the time of discharge but rather improve the long-term adherence to the cardiac medications initiated at discharge.

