#### Secondary Outcomes

Class-specific adherence (defined as a dichotomous outcome) will also be independently defined as PDC ≥80% for a given drug class at 1 year from discharge. Class-specific medication persistence (defined as a dichotomous outcome) will also be independently defined as having claims for any type of medication within that class from discharge date through the following 365 days with no period of 30 days or more without supply (ie, a discontinuation). The number of unique cardiac medication classes (range, 1-4) filled by a patient at their index fill will also be modelled to investigate whether either intervention meaningfully altered the number of medication classes per patient. Additionally, at the time of a patient’s index fill, we will measure the number of days supplied per medication class and the average number of days supplied across all unique medication classes — both outcomes will be dichotomized (ie, ≥90 days supplied versus <90 days supplied).

In addition to medication adherence–based and persistence-based outcomes, we will assess health care utilization and adverse clinical outcomes at 365 days from discharge including the frequency of outpatient primary care visits, frequency of outpatient cardiology visits, hospitalization for cardiovascular disease, hospitalization due to repeat acute MI, hospitalization due to stroke, repeat cardiac catheterization, coronary revascularization, and death. For both visit-based outcomes, visits occurring on the same day as discharge will be excluded.

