### Limitations

While this study proposal highlights the evaluation of a simple, yet novel, approach to improve cardiac medication adherence post-MI, there are methodological limitations. First, the use of administrative databases limits (1) the evaluation of prescription fills rather than swallowing of pills and (2) the assessment of medications and patients not covered by the ODB plan, including aspirin and those <65 years old, respectively. Second, while the interrupted time series analysis can support causal inference, the design is not as robust as an RCT. We do plan to collect appropriate province-wide data throughout this study to inform the design of a future randomized trial. Finally, it is acknowledged that some patients who are classified as nonadherent may have moved away from Ontario, and thus, their prescription claims may be under a different provincial plan for part of the follow-up, leading to potential underestimation of their cardiac medication adherence. The information obtained from this study will help inform the design of a multicenter RCT as an alternative approach to evaluate this proposed intervention.

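### Longer fills can by themselves lift the average-PDC primary outcome through supply left over after a drug is stopped; the plan needs sensitivity analyses that bound this

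*Protocol article*

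**What the plan says.** All references are to the protocol article.

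- **Standardized Discharge Prescription Forms:** "The revised prescription form has a default of a 90-day supply with 3 repeats for recommended cardiac medications". The intervention therefore sets the days supplied at each fill.
- **Primary Outcome:** "The primary outcome will be long-term cardiac medication adherence assessed at 365 days from discharge". PDC is computed per class from dispensing claims, averaged and cut at 80%: "Patients with an average PDC ≥80% among those medication classes dispensed at their index fill will be considered as adherent". For patients who die in the year, "their PDC per class will be calculated over the time elapsed (in days) between their index fill and death date".
- **Secondary Outcomes:** the number of classes averaged runs from 1 to 4. Class-specific PDC of at least 80% and days supplied at the index fill are secondary outcomes. So is class-specific persistence, which requires "no period of 30 days or more without supply (ie, a discontinuation").
- **Primary Outcome Analysis:** the effect is read as a change in level and slope from September 2017. All other Ontario hospitals, which receive no intervention, form the control series.
- **Limitations:** the databases allow only "the evaluation of prescription fills rather than swallowing of pills". This is given as a general limit of administrative data.

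**The concern.** PDC counts days supplied, and days supplied per fill is what the intervention changes. When a patient stops a drug, the unused remainder of the last fill is still counted as covered. That remainder can be up to 90 days after a 90-day fill, but no more than 30 after a 30-day fill. Averaging over classes lets the remainder in one class carry a patient over 80%.

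Any such gain starts when the forms and education start, so it would appear as the level change that the trial tests. Control hospitals get neither component, so a flat control series does not rule it out. Case-mix adjustment does not touch it either. The Discussion projects fewer cardiac events from better adherence, but leftover tablets prevent none. A reader therefore needs to know how much of a level change fill length alone could cause.

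**Working it through.** The plan gives no figure for this mechanism, so there is none to reproduce. The benchmark is the 10-point level change in the Power Calculation section.

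**Inputs from the article:** 365-day window; 80% cut (0.8 × 365 = 292 days); 1 to 4 classes; 90-day default. On current practice it says: "prescriptions covering ≥90 days are currently provided to only 21% of all cardiac patients and to no more than 54% of MI patients".

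**Assumptions:** usual-care fills of 30 days (the article gives no usual-care fill length; 60 days and mixed patterns are also tried), on-time refills, and the stopping rates below.

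**1. One class abandoned after its first fill.** Average = [(k − 1) × PDC of the others + days supplied/365] / k.

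- k = 4, others at 100%: (3 + 30/365)/4 = 77.1%; (3 + 60/365)/4 = 79.1%; (3 + 90/365)/4 = 81.2%.
- The other three must average at least (3.2 − 90/365)/3 = 98.45%. At 95% the 90-day average is 77.4%, which is not adherent.
- Best case with 90 days: k = 3, 74.9%; k = 2, 62.3%; k = 1, 24.7%. A first fill alone cannot tip these patients.

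**2. Later stopping.** Covered days = stopping day rounded up to a whole fill, capped at 365. With the other classes at 100%, a patient is non-adherent on 30-day fills but adherent on 90-day fills if one class is stopped on these days:

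| Classes | Stopping days that tip |
|---|---|
| 4 | 1–60 |
| 3 | 91–120 |
| 2 | 181–210 |
| 1 | none |

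No stopping day tipped the other way. With the others at 95% or 90% the windows move, and for some class counts they disappear.

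**3. Illustrative size.** 400,000 simulated patients per setting; stopping uniform within days 0–90 and 90–365; 30% of patients stop all classes together; pill-taking identical under each pattern. Setting A: 5% stop a class by day 90 and 20% by day 365. Setting B: 10% and 30%. Changes in percentage points, A / B:

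| Move to 90-day fills from | Outcome | 2 classes | 3 classes | 4 classes |
|---|---|---|---|---|
| 30 days throughout | average | +2.1 / +2.6 | +3.4 / +4.2 | +7.6 / +11.5 |
| 30 days throughout | every class | 0.0 / 0.0 | 0.0 / 0.0 | 0.0 / 0.0 |
| 60 days throughout | average | −0.5 / −0.6 | +2.3 / +2.6 | +6.7 / +10.1 |
| 60 days throughout | every class | −2.5 / −3.0 | −3.1 / −3.5 | −3.4 / −3.6 |
| 30-day first fill, then 90 | average | +0.9 / +0.9 | +2.0 / +2.2 | +3.3 / +5.1 |
| 30-day first fill, then 90 | every class | −5.0 / −6.1 | −6.2 / −7.1 | −7.0 / −7.3 |

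Crossing the two early and late stopping rates widens the first row to 1.3–11.9. If only 46% change fill length (100 − 54), that row under A and B scales to 0.46 × 2.1 = 1.0 up to 0.46 × 11.5 = 5.3 points.

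The every-class rule is neutral for 30 versus 90 days because both need a refill at day 270 to reach 292 days. A 60-day pattern reaches 292 with the fill at day 240, so the rule is not neutral there.

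**4. Crediting the last fill only if a refill follows.** For 30 to 90 days throughout, the average outcome then changes by −3.0 / −3.6 (2 classes), −3.5 / −4.0 (3) and −1.7 / −2.3 (4). This errs against longer fills, so with full credit it brackets the null.

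**5. Related rules.**

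- Death: a single fill keeps PDC at or above 80% until 90/0.8 = 112.5 days, against 30/0.8 = 37.5. The last adherent day of death is 112 versus 37, even with one class.
- Persistence: with on-time refills, the last fill needed is at day 270 on 90-day supply (covered to 360). On 30-day supply it is at day 330, since a last fill at day 300 leaves 35 uncovered days. Stopping between days 270 and 330 therefore counts as persistent only on long fills: 15% × 60/275 = 3.3 points under A and 20% × 60/275 = 4.4 under B.

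**The case against.** The strongest reply is that the size is unknown. Class mix, stopping times and usual-care fill lengths are not in the article, and the 54% describes discharge prescriptions, not later refills. If usual care already moves to 90-day refills after a short first fill, the gain falls to about 1 to 5 points before any scaling. From 60-day fills with two classes it is about zero or slightly negative. All of this stands, and it limits the size rather than removing the mechanism.

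The article also has partial safeguards. Class-specific adherence and days supplied at the index fill are prespecified, and fills versus ingestion is disclosed. A gap between the average and class-specific results would be a warning. But these items neither correct the primary outcome nor condition its interpretation.

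Two remedies might suggest themselves and should be resisted. Making PDC of at least 80% in every class the primary outcome, or requiring it to agree before benefit is claimed, could swap a bias for the intervention for one against it (step 3). Dropping early deaths would condition on an event after the intervention that is itself a study outcome.

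A reader might also take the Limitations section to assume that the fill-versus-ingestion gap is equal across groups. It does not say so; it is silent on whether the gap differs.

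**Conclusion.** The point holds as a matter of what can happen. Leftover supply from longer fills can raise the average-PDC outcome without any change in pill-taking, from launch onward, and the control series cannot show it.

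A reader might infer that the intervention will raise the outcome this way, or that one abandoned 90-day fill generally tips a patient over 80%. The document supports neither. The first-fill case needs exactly four classes with the other three at 98.45% or more. Two- and three-class patients tip only through later stopping, and one-class patients do not tip for 30 versus 90 days.

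The size is about 2 to 12 points for a complete move from 30- to 90-day fills under the assumed stopping rates, and about 1 to 5 if 46% of patients move. Both figures rest on assumed 30-day usual-care fills, on-time refills and stopping rates that the article does not give. Against a 10-point target this is large enough to matter for interpretation. It does not require a different primary outcome.

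**What to change.** Keep the average-PDC primary outcome and prespecify the following on the ODB data.

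1. Recompute average PDC and persistence with each class's last fill credited (a) in full and (b) only if a later refill follows, looking at least one fill length past day 365. The last discharges are in August 2018 and analysis is expected in late 2020, so those claims should be available.
2. Report PDC of at least 80% in every index class alongside, stating that it is neutral only for 30 versus 90 days.
3. Show decedents separately, or repeat the analysis under an alternative decedent rule. Do not simply drop early deaths from the primary analysis.
4. State that a level change will be read as improved adherence only to the extent that it exceeds what fill length alone can produce. Estimate that amount from the class counts and fill lengths seen before the intervention, because (a) and (b) need not enclose zero for every refill pattern. For a 30-day first fill followed by 90-day refills, rule (b) still gave +0.7 to +2.3 points with two to four classes under settings A and B.

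The cost is modest extra coding, a short extension of the claims window, and a wider or somewhat less favourable range around the effect.
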